### Data Collection and Sources of Information

Data regarding the total number of visits will be obtained from the Primary Care Services Information Technologies System (ie, Sistemes d’Informació dels Serveis d’Atenció Primària in Catalan), which belongs to the Catalan Institute of Health in Barcelona, Spain.

The asynchronous, mobile text-based communication platform that is made available by AGH makes it possible to collect information on cases that involve a written query. User data will be obtained from the platform’s database, and users will remain anonymous. The information collected will include age, gender, the date and time of the query, and the answer to the query. In addition, all the professionals involved in the study will sign a document, in which they will agree to respect data confidentiality.

After a response from a health care professional is received, users will be able to respond to a questionnaire, in which they can evaluate the quality of the service and their level of satisfaction (Multimedia Appendix 1). The data in this questionnaire will be collected and processed by AGH.

### Statistical Analysis

Spreadsheets will be used to record the means and medians of various data. Statistical analyses will be performed on the data that users will enter in the registration form and the data collected from the questionnaire. The questionnaire will be sent to participants after their consultation concludes. The questionnaire consists of multiple-choice questions, which makes it possible to assign a numerical value to various responses. These values will be used in the corresponding statistical analyses.

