**Methods:**

The quasiexperimental study will compare the number of face-to-face consultations to the number of consultations conducted on XatJove Anoia, as part of the Health in Schools program in the Anoia region. The study will involve the use of a new communication platform (ie, XatJove Anoia) for health care professionals and adolescents, and data on the number of face-to-face consultations will be collected as part of the same program in another region. Data will be collected from secondary schools during the academic year 2020-2021. Statistical analyses will be performed on the data that users will enter in the registration form. These data will be collected by means of a questionnaire, which will be submitted once the questionnaire is closed. The questionnaire will consist of multiple-choice questions, which will allow numerical values to be assigned to various responses in order to carry out statistical analyses.

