According to a pilot study, cystitis and contraceptive problems are among the top 10 reasons why patients have used a web-based tool to conduct a consultation [8]. Although these conditions can be embarrassing and difficult to talk about, it is important that they are dealt with by health care professionals. If ignored, these conditions can lead to serious, unwanted, and costly complications (eg, a failure to use contraception can lead to unwanted pregnancies and sexually transmitted diseases) [9,10]. The fact that users have routinely reported these problems by means of digital health interventions, such as e-consulta (ie, an asynchronous teleconsulting service for primary care professionals and health service users that is connected to primary care electronic medical records), is a positive sign with regard to the greater use of health services for sensitive and serious conditions. As an anonymous digital health intervention, XatJove has the potential to address the inefficient costs resulting from the underutilization of health services for embarrassing and stigmatized disorders.

Due to the current climate of the health crisis caused by the COVID-19 pandemic [11] and the need to reduce the risk of infection, it makes more sense than ever to avoid face-to-face consultations with nursing staff in schools and primary care center visits by young people. It should be noted that this does not mean that there will be a reduction in the number of consultations for health-related issues and the number of school programs. On the contrary, the health crisis is expected to generate an increase in the need for emotional support for young people, and such support requires tools that allow for the quick use of technology (ie, technology that adolescents and primary care center professionals are familiar with and use regularly).

The main objective of this protocol is to describe a quasiexperimental study that shows that the use of mobile phones and messaging apps leads to an increase in the number of health consultations for adolescents aged between 12 and 16 years, as part of the Health and School program in the Anoia region. The study also seeks to evaluate the degree of satisfaction among XatJove users via an electronic survey.

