## Methods

### Study Design

A quasiexperimental study that compares the total number of face-to-face consultations and XatJove consultations will be conducted as part of the Health and School program in the Anoia region (ie, the intervention group) during the 2020-2021 academic year. Data on the number of face-to-face consultations will be collected from the same program in the Osona region (ie, the control group). Problems that affect adolescents and relate to mental health, emotional and sexual health, drug use, alcohol, and tobacco will be recorded. The study population will include adolescents aged between 12 and 16 years who attend secondary schools in the Anoia region. We will use a pragmatic sample of 100 XatJove consultations. The total number of visits (ie, face-to-face visits and XatJove visits) that relate to the Health and School program in the Anoia region during the 2020-2021 academic year will be recorded.

The following variables will be recorded: (1) universal variables, including gender and age; (2) dependent variables, including the total number of visits (ie, face-to-face visits and XatJove visits) that relate to the Health and School program; and (3) independent variables, including the topic of consultations (ie, consultations for sexual health, alcohol, drugs, eating disorders, bullying, domestic abuse, mental health, COVID-19, and other topics).

To learn more about the usefulness of XatJove, students will be asked to participate in a follow-up study that involves a focus group.

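### The data named for statistical analysis cannot address the main objective, no analysis of the visit counts is stated, and the contrast is worded so that it may compare channels rather than regions

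*Protocol article*

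**What the plan says.** The Introduction of the protocol article gives the main objective as showing that "the use of mobile phones and messaging apps leads to an increase in the number of health consultations" among 12- to 16-year-olds. Satisfaction among users is an additional aim.

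The Study Design section calls Anoia the intervention group and says: "Data on the number of face-to-face consultations will be collected from the same program in the Osona region (ie, the control group"). It lists "dependent variables, including the total number of visits (ie, face-to-face visits and XatJove visits") for the programme, and then "independent variables, including the topic of consultations". Region is not in the list. The same section describes a study that "compares the total number of face-to-face consultations and XatJove consultations".

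The Abstract (Methods) says the study will "compare the number of face-to-face consultations to the number of consultations conducted on XatJove Anoia". Its next sentence adds that face-to-face counts will be collected in another region.

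Data Collection and Sources of Information draws total visits from the primary care information system. User data come from the platform's database, and the satisfaction questionnaire follows a professional's reply on the platform.

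The Statistical Analysis section says that means and medians of unspecified data will be recorded in spreadsheets, and that "Statistical analyses will be performed on the data that users will enter in the registration form and the data collected from the questionnaire". It mentions neither visit counts nor Osona, and no comparison between groups.

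**The concern.** The objective, the design and the stated analysis do not line up, in three ways.

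- **Data source.** The objective concerns how many consultations take place. The data named for analysis describe people who have already used the chat service.
- **Contrast.** A comparison of chat counts with face-to-face counts measures which channel is used. It does not measure whether consultations increased.
- **Explanatory variable.** Topic is known only once a consultation has happened, so it cannot explain how many occur. The exposure that separates the two groups is region.

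At stake is the main result. Analysing only the data named would give user characteristics and satisfaction scores. Analysing the contrast as the Abstract words it could suggest success when total consultations have not risen.

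**Working it through.** The document states no effect size, rate, significance level or power. Its only sample figure is a pragmatic 100 XatJove consultations. There is therefore no planned figure to reproduce, and the check is mainly a comparison of sections.

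**Step 1: can the named data supply the comparison?**

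| Needed for the main objective | Source given in Data Collection | Named in Statistical Analysis? |
|---|---|---|
| Anoia face-to-face visits | Primary care information system | No |
| Anoia XatJove visits | Information system (within total visits); queries also logged in the platform database | Registration form and questionnaire only |
| Osona face-to-face visits | Not tied to a source by name; the information system is the source given for visit totals | No |

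The Limitations section says the service is offered only to students at secondary schools in Anoia. The registration form and questionnaire therefore contribute no Osona observations and no face-to-face visits. Both an Anoia-versus-Osona contrast and a face-to-face-versus-XatJove contrast need counts that these data lack.

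**Step 2: what would each contrast show?** Let F_A and X_A be Anoia's face-to-face and XatJove counts, F_O Osona's face-to-face count, and N_A and N_O the enrolled students.

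- Channel ratio = X_A / F_A
- Regional rate ratio = [(F_A + X_A) / N_A] / [F_O / N_O]

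All counts below are assumed, since the document gives none. Enrolment is taken as equal (N_A = N_O), so it cancels, and F_O = 200 throughout.

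| Scenario | F_A | X_A | Channel ratio | Regional ratio |
|---|---|---|---|---|
| Substitution, a quarter by chat | 150 | 50 | 50/150 = 0.33 | 200/200 = 1.00 |
| Substitution, half by chat | 100 | 100 | 100/100 = 1.00 | 200/200 = 1.00 |
| Substitution, 60% by chat | 80 | 120 | 120/80 = 1.50 | 200/200 = 1.00 |
| Substitution, three quarters by chat | 50 | 150 | 150/50 = 3.00 | 200/200 = 1.00 |
| Real increase, face-to-face unchanged | 200 | 100 | 100/200 = 0.50 | 300/200 = 1.50 |

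Under pure substitution the channel ratio runs from 0.33 to 3.00 while the regional ratio stays at 1.00. In the last row consultations are half as many again as in Osona, yet the channel ratio is 0.50. The channel ratio can therefore mislead in either direction. Substitution is plausible on the document's own account: the Introduction sees reason to avoid face-to-face consultations during the pandemic, and the Discussion reports that web-based tools reduced them in previous studies.

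**Step 3: what could be estimated from one total per region?** A model with an intercept and a region term has 2 parameters for 2 observations, which leaves 2 − 2 = 0 residual degrees of freedom. Overdispersion cannot be estimated without finer counts.

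**The case against.** This is a journal article, and a full protocol or analysis plan may exist. The choice of model, offset and covariates is properly left to such a document and is not criticised here.

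A reader might infer that the regional comparison will never be run, or that region has been excluded from it. The document does not support that:

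- The Statistical Analysis section does not say that only the user data will be analysed, and its means and medians of unspecified data could loosely include visits.
- Study Design names the two regions as groups and makes total visits a dependent variable, and Data Collection gives a source for visit totals. The comparison is intended.
- The variable list is introduced as open-ended, so region is omitted rather than ruled out. The list also stands in Study Design, not in the Statistical Analysis section.

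A reader might also infer a clean contradiction between the Abstract and Methods. That is too strong. The Study Design sentence is open to the same channel-against-channel reading, and the Abstract does mention data from another region. It is one ambiguity in two places.

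The Discussion calls the study a pilot, which lowers the precision expected. It does not change which data can answer the stated objective.

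What remains is that the article does more than leave out detail. In two places it names data for analysis, and those data serve the satisfaction aim and not the main one. An analysis plan with the right comparison would still leave this text to be corrected.

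**Conclusion.** The concern holds in this form: no analysis of the visit counts that carry the main objective is stated, the data that are named cannot replace them, and the contrast is worded ambiguously. Topic is labelled as an independent variable while region goes unlisted.

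Followed as written, the plan gives no estimate for the main objective, or possibly a misleading one. The finding on data sources follows from the text alone and needs no assumed figure. It relies on the statement that the service is offered only in Anoia; because users are anonymous, the article concedes that eligibility cannot be verified. The size of the distortion is illustrative: the gap between 1.50 and 1.00 depends on assumed counts, equal enrolment and pure substitution, and no such figures are in the document. The correction should be made before the data are analysed.

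**What to change.** Put one consistent statement in the Abstract, Study Design and Statistical Analysis:

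- The primary analysis compares total programme visits in Anoia (face-to-face plus XatJove) with total face-to-face visits in Osona over the 2020-2021 academic year, as rates per enrolled student.
- Region is the independent variable, and the result is a rate ratio with 95% CI.
- The source of each count is named, including which system supplies the XatJove count.
- The split by channel and the breakdown by topic are descriptive.
- The questionnaire serves the satisfaction objective.

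Correcting the Abstract alone would leave the ambiguity in Study Design.

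The wording costs a few sentences, but the analysis is not entirely free. The document does not list enrolment numbers as collected, so they must be obtained for both regions. School-level or monthly counts are needed if overdispersion is to be estimated. With one region per arm, the interval will not capture differences between regions that are unrelated to XatJove; this should be stated as a limitation.

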### Limitations of the Study

It is possible that an insufficient number of users will rate the service and respond to the questionnaire. If this happens, the deadline for collecting data will be extended.

Although it will be possible to send questions via XatJove 24 hours per day, answers will only be sent during specific time slots (ie, from 8 AM to 8 PM, including weekends). This may limit the accessibility of the service. However, any inquiries made outside of this time slot will be answered by medical professionals at the start of their next working day.

Since XatJove is an anonymized service, it will not be possible to verify whether users meet the inclusion criteria. Nevertheless, the service will only be offered to students who attend secondary schools in Anoia.

### Ethical Considerations

The Institut Universitari d’Investigació en Atenció Primària Jordi Gol independent ethics committee in Barcelona, Spain approved the trial study protocol (code 20/137-P). Written informed consent will be requested from all patients who participate in the study. The study was registered on the ClinicalTrial.gov registry (NCT04562350) on September 24, 2020.

### Availability of Data and Materials

All principal investigators of the study will have access to the complete dataset. The datasets generated and analyzed during the study will be made available by the corresponding author. The results generated during the study will be published in peer-reviewed journals and presented at national/international congresses.

The study has been designed in accordance with the CONSORT (Consolidated Standards of Reporting Trials) guidelines. The registration of the study on ClinicalTrials.gov is expected to facilitate transparency and reporting.

## Results

The study is projected to start at the beginning of November 2020 and finish in June 2021, which is when data analysis is expected to start.

## Discussion

This aim of the pilot quasiexperimental study is to investigate the use of a mobile phone health chat service for adolescents from secondary schools in Anoia and nursing professionals from primary care centers in the same region.

The various studies that we previously participated in have shown that the use of a web-based communication tool for patients and professionals reduces the number of face-to-face visits [12,13], which is a very positive aspect with regard to the COVID-19 pandemic. Furthermore, the results of the study and the long-term and short-term impacts of XatJove will be used to revise the Health and School program, which is offered by the Department of Health. In other words, XatJove is a tool that will serve in the review of existing protocols. Web-based visits and consultations are gaining in popularity in the new health care environment that has resulted from the COVID-19 pandemic.

Web-based consultations can help with avoiding self-diagnoses, as it is common for people to search for information on the internet, which is not always a reliable source. Current evidence points to the importance of innovating and improving the treatment processes offered by health and school programs. One of our study’s strengths is that the results will be obtained from usual clinical practices, without having to implement any considerable organizational or structural changes.

## Appendix

Multimedia Appendix 1 Questionnaire for evaluating the quality of the service.

## Abbreviations

AGH: Abi Global Health
CONSORT: Consolidated Standards of Reporting Trials
